### Participants

Eligible clusters (“work groups”) are those stores with an online department, located within 1.5 hours’ drive of Sydney or Brisbane, Australia, which are the cities where the facilitators are based. Random sampling within eligible work groups will account for work groups with varying sales volumes and service offerings (eg, delivery to a customer’s vehicle parked outside the store, loading orders onto trucks for home delivery, and/or collection of orders by a third-party delivery driver through a service such as Uber). Managers of work groups are recruited to the study if they are the manager of the online department or store associated with the individual work group or are a manager responsible for the group of stores that the individual store or work group sits within.

Facilitators are allocated to work groups in a manner that replicates real-world conditions for toolkit implementation. These facilitators work in the organization’s health and safety team in the states where the intervention is conducted and possess a range of qualifications and experience, from a background in store management and operations through to degree-qualified health and safety professionals with varying years of experience.

### Recruitment

A total of 18 work groups (9 intervention and 9 control) will be recruited to the study. All work groups will be located within 1.5 hours’ travel time of Sydney or Brisbane, Australia. Settings range from inner urban to semirural locations. The number of work groups required for the study was determined based on the average number of employees in each work group and typical response rates to employee engagement surveys in stores, which are usually 20%-30%.

Stores are recruited to the study through consultation with the resource capacity management unit within the organization. This unit determines which stores are already engaged in other activities which would limit their ability to participate. This unit will then facilitate communication with the management of the groups of stores deemed eligible for participation. This management team then facilitates communication with the stores in their group that are selected for participation via the randomization process. Recruitment of stores continues until the required sample size is achieved.

Individual participants within a work group are eligible for recruitment to the study if they work some or all their work time in the online department, are a manager of an eligible online department or the store, or a manager overseeing an eligible store or “group” of 10-11 stores. These individual employees are involved in the study through completion of the APHIRM toolkit survey and feedback and consultation processes on identified sources of risk and action plans. Recruitment materials and advertising will be distributed through channels only accessible to those employees working in the online department. This is to prevent inadvertent recruitment of employees working in other departments in the store. These channels include the digital discussion board used to communicate with online employees and the posting of physical flyers on the noticeboards in the online room of the store. Informed consent statements and information on the study are provided to participants when they access the online portal used to administer the toolkit.

Recruitment of managers will be conducted through meeting invitations for briefing sessions aimed at communicating the study or providing updates about the study’s progress. Informed consent statements are provided to these managers at the commencement of the sessions.

RMT members for each work group are recruited through the same channels as individual participants in the study. Each work group is encouraged to recruit a minimum of 3 RMT members, which is intended to ensure that at least 2 RMT members are available to participate in each of the monthly facilitated sessions in store.

### Intervention

Clusters in the experimental group will implement the APHIRM toolkit processes and procedures with the guidance of a facilitator. The APHIRM toolkit guides work groups through the steps of the risk management cycle to address the sources of physical and psychosocial hazards that contribute to WMSDs and MHPs. Each step of toolkit implementation is delivered as a face-to-face session lasting up to 2 hours. Resources used to facilitate these sessions are freely available on the official website [47].

The first step of the process involves identifying members of the work group to act as representatives for their peers during toolkit implementation. This group is known as an RMT.

In the second step, the work group is invited to complete a survey that rates exposure to physical and psychosocial hazards, musculoskeletal pain or discomfort, and stress levels. The survey forms the hazard identification and risk assessment component of the risk management process. This survey is administered through an online portal, hosted as part of the APHIRM toolkit on its official website [47]. This enables the completion of surveys on any computer or mobile device. The survey is anonymous at the individual level, with responses aggregated to the work group (store) level.

In the third step, the results of the survey are provided to the work group, who then provide input on the work-related sources of risk relating to the identified hazards. Over the course of 10 monthly face-to-face sessions, the facilitator guides the RMT through the development and implementation of an action plan to address the sources of risk. It is anticipated that RMTs will identify a combination of actions that are specific to their individual store, as well as actions that are implemented in every store and thus require assistance from personnel above the individual store level to address.

The implementation of actions at the store level is expected to assist in differentiating intervention stores from control stores when measuring hazard severity at follow-up. It is also possible that the act of engaging RMTs from the intervention stores in the development of above-store actions will have an impact on hazard severity scores at follow-up, greater than the impact of the actual implementation of changes to the system of work. The impacts of these changes are expected to be felt by control and intervention stores equally if they are implemented before follow-up data collection. Many changes at the system of work level are unlikely to be implemented before follow-up, further allowing for differentiation between control and intervention groups. If significant changes are implemented in both control and intervention stores during the study, and it is determined that these changes may influence the results of the study, an additional survey will be conducted following the implementation of this change. This will be followed by the planned survey at the 12-month follow-up. This 12-month follow-up comprises the fourth step of the intervention, in which the survey is repeated approximately 12 months after the initial survey. These results are also communicated to the work group, along with an invitation to provide feedback on their perceived effectiveness of the action plan.

In parallel with implementation of the APHIRM toolkit, managers who are responsible for the online department for each intervention work group will be invited to participate in a questionnaire to evaluate their SoC. This will be conducted at commencement of the intervention, then every 3 months during the intervention, and on conclusion of the study, approximately 12 months following commencement.

Clusters in the control arm do not implement the APHIRM toolkit. These work groups only complete the APHIRM toolkit survey at commencement and conclusion of the study, and the managers associated with these work groups complete the SoC assessment every 3 months during the intervention period. These work groups otherwise receive the usual care and safety support from their management team, including the safety professionals who usually support the work group. This includes conducting a monthly safety meeting with the work group’s safety committee, performing safety inspections, and participating in other routine activities relating to managing workplace health and safety in the store. Work groups assigned to the control arm are not prevented from implementing changes to address sources of MSD or MHP risk.

Figure 1 illustrates the structure and timing of the intervention and control work groups’ involvement in the study for the purposes of providing comparison data.

**Figure 1 figure1:**
[figure not shown]
Structure and timing of intervention activities. APHIRM: A Participatory Hazard Identification and Risk Management; RMT: risk management team.

Facilitators from the organization’s health and safety team are trained in the administration of the intervention by a member of the research team. This includes training on the procedures to facilitate each of the sessions that comprise the intervention, as well as data collection and ethics compliance procedures. The training is delivered using the resources provided in the APHIRM toolkit. One member of the research team and one member of the health and safety team have completed the 1-day APHIRM training workshop offered by La Trobe University on establishing and delivering the APHIRM toolkit in workplaces.

Adherence to toolkit procedures is monitored by reviewing the outputs of the work group, which are recorded in the work group’s toolkit portal on APHIRM’s official website [47]. Facilitators use an online notebook to record observations from each session, including how clusters use the resources from the APHIRM toolkit, fidelity to the toolkit procedures, and other observations that are important to the process evaluation completed as part of the study.

If the data provided at the conclusion of a session indicate that procedures may not have been correctly followed, a member of the research team will complete a follow-up session with that facilitator and the work group in question to review and prepare the work group for the next session and step in the intervention.

### Outcomes

#### Quantitative Outcomes

Quantitative data are collected anonymously at the individual level and are therefore aggregated and analyzed at the work group level. Baseline and follow-up data are collected at the same time of the year (August/September), which assists in accounting for seasonal variation and avoids potential impacts on response rates by avoiding busy trading periods.

#### Primary Outcomes

Previous research has confirmed the validity of the toolkit survey [29] and generated evidence to support the toolkit’s effectiveness at reducing exposure to hazards that contribute to WMSDs and MHPs [27,28]. The primary outcome measures for this study are changes in the mean severity ratings for physical and psychosocial hazards, based on the relevant items from the APHIRM toolkit survey. These data are self-reported by members of the work group. Mean severity ratings for each group of hazard items are calculated at the cluster level (ie, each work group), by calculating the difference between baseline and follow-up means. All primary outcome measures will be assessed for mean change by cluster, which will be analyzed using ANCOVA, comparing outcomes for the 2 arms. Outcomes for each work group will also be compared to identify potential outliers. Data will be cleaned and examined for normal distribution prior to analysis. Differences in cluster sizes will be identified and accounted for using suitable analysis, which will be reported with the results.

#### Calculation of Severity Ratings for Physical Hazard Measures

A total of 12 survey items relate to physical (biomechanical) hazards that may influence MSD risk. Hazard measures include items related to force, repetition, and awkward and sustained postures, and vibration. Respondents rate their exposure to each hazard, in the last 6 months, on a scale from 1 (almost never) to 5 (almost always). A mean rating is calculated for all 12 survey items relating to physical hazard exposures.

#### Calculation of Severity Ratings for Psychosocial Hazard Measures

A mean rating for each cluster is calculated for all 44 survey items relating to psychosocial hazards. Examples of psychosocial hazard measures include items relating to control over the pace and content of work, role clarity, and reward and recognition.

#### Secondary Outcomes: Score for Self-Rated Pain and Discomfort

Using the measures in the APHIRM toolkit survey, participants rate the frequency and severity of their musculoskeletal pain and discomfort (in the last 6 months) in each of 5 body regions: neck/shoulders, arms, hands/fingers, middle/lower back, and hips/bottom/legs/feet. For example, “In the last six months, how often have you felt discomfort or pain in your neck or shoulders?” Response options range from 0 (never) to 4 (almost always). Any response equal to or greater than 1 (occasionally) then generates an additional question, for example “In the last six months, how bad was the discomfort or pain in your neck or shoulders?” Response options range from 1 (mild) to 3 (severe). A score out of 12 (4 × 3) is calculated for each body region and summed to produce a score out of 60 for each participant reporting any pain or discomfort. The change in mean scores between baseline and follow-up is used to evaluate outcomes.

#### Action Plan Implementation

Data on action plan implementation will be collected via inputs and updates to the action plan created and updated for each store and managed through the toolkit portal. Actions will be classified as “completed,” “in progress,” or “not started” through the review of the action plan during monthly sessions conducted with the facilitator and the work group. Actions will also be classified as “higher-order” actions, involving hazard elimination, substitution, or engineering actions, or “lower-order” actions, involving administrative actions such as process changes.

Actions will be classified as “store-level” or “above-store-level” actions by the facilitation team, partly to determine which actions require escalation above the store’s management to be addressed, and partly to evaluate how many store-level actions achieve “completed” status, compared with actions classified as above-store-level. This data will be validated by the research team through an independent review of action plan data collected by the APHIRM toolkit online portal. The count of each action and its classification in each of the above dimensions at the end of the 12-month study for each cluster will be reported.

#### Additional Outcome Measure

Managers’ SoC progression will be measured using the questionnaire included in Multimedia Appendix 1. The questionnaire will be administered every 3 months for the duration of the study via scheduled management meetings. Measurement is conducted for each relevant manager group: all the managers directly responsible for a work group in a store (online department and store managers), and managers with responsibility for groups of stores, known as “above-store managers.” Because of this, data for a manager with responsibility above a single store level may be considered when evaluating the implementation process for multiple stores under their direction, while SoC data for a store manager would only be considered in the process evaluation for the individual store under their management.

Movement through the SoC at each timepoint will be reported, as well as the absolute difference in stages, if any, from baseline to follow-up (ie, the total number of stages the work group’s managers moved through during the study period and whether movement was progressive or regressive through the SoC). This survey tool was selected as it has been previously validated as an instrument sensitive to detecting both workers’ and managers’ readiness to implement changes to address physical and psychosocial risk factors in the workplace [36,50,51]. SoC data will be collected and managed using REDCap (Research Electronic Data Capture; Vanderbilt University) electronic data capture tools hosted at La Trobe University [52,53]. REDCap is a secure, web-based software platform designed to support data capture for research studies.

A summary of outcome measures, analysis metrics, methods of aggregation, and measurement timepoints is included in Table 1.

**Table 1 table1:** Study measures, metrics, methods of aggregation, and frequency of measurement.

Primary or secondary	Outcome measure	Analysis metric	Method of aggregation	Participants providing data	Timepoints
Primary	Physical hazard measures	Change from baseline	Mean	Individual employees from each work group	At commencement and 12 months after commencement
Primary	Psychosocial hazard measures	Change from baseline	Mean	Individual employees from each work group	At commencement and 12 months after commencement
Secondary	Change in self-rated pain and discomfort	Change from baseline	Mean	Individual employees from each work group	At commencement and 12 months after commencement
Secondary	Change in self-rated stress score	Change from baseline	Mean	Individual employees from each work group	At commencement and 12 months after commencement
Secondary	Action plan implementation	Number of actions implemented by action status or type	Count	Risk management teams from intervention stores	At the conclusion of the study
Additional	Stage of change progression	Change from baseline	Difference between initial and final values; changes between each measurement period	Store managers (allocated directly to a store or work group); above-store managers (overseeing multiple work groups)	At commencement, and every 3 months after commencement

#### Process Evaluation

Data will be collected to enable a process evaluation of the implementation of the toolkit in intervention work groups. Observations and reflections will be recorded by facilitators after each interaction with participating clusters using an online notebook and synthesized to enable evaluation of the intervention using the “Reach, Effectiveness, Adoption, Implementation, and Maintenance” framework [54]. Observation themes will include the extent and nature of engagement of participants; reflections and feedback on participants’ comments about the intervention process and their satisfaction with the process; participants’ willingness to adopt the toolkit process and identified action plans; adherence to and deviation from toolkit processes; maintenance of implementation of toolkit processes; and actions that were implemented, to the extent possible considering the duration of the study. Observations will be recorded after each face-to-face meeting with each cluster, noting which resources from the APHIRM toolkit were used and how the resources were used. Interactions with members of the RMT or store-level managers for each cluster will be noted. Observations for above-store managers will be either linked to the clusters relevant to the observation being recorded or recorded as a separate record where there is no clear link between the interaction and specific clusters. These observations will be recorded in an online notebook by facilitators and monitored and reviewed by the research team.

This data will also be used to evaluate how different clusters use the resources provided in the APHIRM toolkit and how this relates to the cluster’s SoC.

### Sample Size

Sample size calculations were based on primary outcome measures of changes in physical and psychosocial hazard severity ratings. Considerations were made to the organization’s structure when determining the number of clusters and participant numbers in each cluster. Individual stores are organized into “groups” of 10-11 stores, overseen by a group manager, justifying a 3-level cluster design.

Online department numbers were reviewed by store to determine expected cluster size. Additionally, response rates to previous surveys (not connected with the current project) were reviewed and found to be between 20% and 30%. These values were then used to calculate the sample size within each cluster to account for differences in expected recruitment across clusters. The mean cluster size (number of expected participants in a cluster) was set at 15, with a cluster variation of 0.7. If the mean cluster size deviates significantly from the estimated value of 15, this will be identified and accounted for in the statistical analysis and the interpretation of results.

Table 2 sets out the sample size and power calculations for primary and secondary outcomes evaluated in the randomized controlled trial, taking into account the 3-level cluster design at α=.05, intraclass correlation coefficient level 2=0.10; intraclass correlation coefficient level 3=0.05, mean cluster size=15; and estimated cluster variation=0.7, derived using Monte Carlo simulation. A previous study was used to estimate the effect size for exposure to physical hazards, exposure to psychosocial hazards, and self-rated pain and discomfort scores [55]. Results from Rahimi [56] were used to estimate effect sizes for stress scores.

On this basis, it was determined that 9 control and 9 intervention clusters (18 clusters in total) were required to achieve power of 0.8 or more.

**Table 2 table2:** Sample size and power calculations.

Outcome			Mean (SD)		Effect size (*d*)		Groups (level 3), count		Stores (level 2), count		Employees (level 1), approximate n		Power (95% CI)

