**Primary outcomes**													
	Exposure to physical hazards	3.7 (0.6)		0.5		3		18		270		0.870 (0.816-0.910)	
	Exposure to psychosocial hazards	2.4 (0.6)		0.5		3		18		270		0.870 (0.816-0.910)	

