**Secondary outcomes**													
	Pain/discomfort	14.9 (8.3)		4		3		18		270		0.780 (0.753-0.805)	
	Stress	4.02 (2.56)		0.5		3		18		270		0.742 (0.714-0.768)	
	Burnout	4.76 (2.54)		0.5		3		18		270		0.734 (0.706-0.760)	
	Cognitive stress	3.33 (2.57)		0.5		3		18		270		0.745 (0.717-0.771)	

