### Statistical Methods

Baseline characteristics, including baseline values of the primary outcomes, store size (number of employees), and available aggregate demographic measures, will be summarized at the store level and presented descriptively by treatment arm (mean, SD, median, range, or proportion, as appropriate). Data for each cluster will be analyzed to identify potential outliers. Data will be cleaned and examined for normal distribution prior to analysis. The primary outcome measures (physical and psychosocial hazard severity ratings) will be analyzed by variance-weighted cluster-level ANCOVA using posttreatment store means regressed on treatment assignment and baseline store mean, with group fixed effects. Weights will be set to the inverse of the estimated theoretical variance of the cluster means to account for potential unequal cluster sizes. Because there are only 18 clusters (9 per arm) and 3 higher-level strata, estimation of higher-level variance components is unstable, and asymptotic cluster-robust SEs perform poorly. However, analyses using generalized estimating equations will be presented as sensitivity checks, with full disclosure of small-sample limitations.

Data on action plan implementation will be analyzed as categorical data. The count of actions by each status category (eg, “completed,” “in progress,” or “not started”) and categorization as “higher-order” or “lower-order” will be performed for each cluster and compared against the other outcome measures for that cluster.
Data on SoC progression will be analyzed as ordinal data. The median and mode response for the cluster will be determined as the SoC for that cluster at each measurement point. SoC data for store managers and above-store managers will be analyzed separately for each cluster. Progression through the SoC will be evaluated by assessing the number of SoC each group progresses through at each timepoint and overall, from commencement to the conclusion of the study.

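### Table 2 gives power 0.870 for the primary outcomes but 0.734 to 0.745 for three other outcomes with the same stated inputs, so the claim of at least 0.8 is not supported as written

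*Protocol article*

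**What the plan says.** The protocol article (Sample Size) bases the calculation on the two primary outcomes, physical and psychosocial hazard severity. It introduces Table 2 as covering primary and secondary outcomes, "taking into account the 3-level cluster design at α=.05", with "intraclass correlation coefficient level 2=0.10; intraclass correlation coefficient level 3=0.05, mean cluster size=15" and a cluster variation of 0.7, by Monte Carlo simulation. It then states that "it was determined that 9 control and 9 intervention clusters (18 clusters in total) were required to achieve power of 0.8 or more".

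Table 2 has a column headed as effect size d. Every row has 3 groups, 18 stores and about 270 employees.

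| Row | Mean (SD) | Entry under d | Power (95% CI) |
|---|---|---|---|
| Physical hazards (primary) | 3.7 (0.6) | 0.5 | 0.870 (0.816 to 0.910) |
| Psychosocial hazards (primary) | 2.4 (0.6) | 0.5 | 0.870 (0.816 to 0.910) |
| Pain/discomfort | 14.9 (8.3) | 4 | 0.780 (0.753 to 0.805) |
| Stress | 4.02 (2.56) | 0.5 | 0.742 (0.714 to 0.768) |
| Burnout | 4.76 (2.54) | 0.5 | 0.734 (0.706 to 0.760) |
| Cognitive stress | 3.33 (2.57) | 0.5 | 0.745 (0.717 to 0.771) |

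Statistical Methods fixes the primary analysis as "variance-weighted cluster-level ANCOVA using posttreatment store means regressed on treatment assignment and baseline store mean, with group fixed effects".

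**The concern.** If d is standardised, the outcome's mean and SD drop out of the power calculation. Power then depends only on d, alpha, the ICCs, the store sizes and the numbers of stores and groups, and all of these are stated once for the whole table. Five rows with d=0.5 must therefore show one power. They show two, about 0.13 apart and on opposite sides of the 0.8 target.

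The choice of 18 stores rests on the higher figure. A null primary result would be read against a stated power of 0.870 that the article's own table does not reproduce.

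**Working it through.** **1. Is the gap simulation noise?** The printed intervals identify the number of runs. Wilson 95% limits for 174/200 are 0.816 to 0.910, as printed for the primary rows. For 742/1000 they are 0.714 to 0.768, as printed for stress; 734/1000 and 745/1000 also give the printed limits. The rows are thus consistent with 200 runs (primary) and 1000 runs (secondary). For primary against stress:

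z = (0.870 − 0.742) / √(0.870×0.130/200 + 0.742×0.258/1000) = 0.128 / 0.0275 = 4.65.

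The lower primary limit, 0.816, exceeds the highest stress-type limit, 0.771. Noise does not explain the gap.

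**2. Is d in raw points?** Primary: 0.5/0.6 = 0.83 SD, power about 0.96 to 0.97. Stress: 0.5/2.56 = 0.20 SD, power about 0.15 to 0.20. Neither matches its printed value.

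**3. Does the column use one scale?** Pain is entered as 4. With SD 8.3, 4/8.3 = 0.48 SD, so 4 must be raw points. At 0.48 SD power should be slightly below the d=0.5 rows, but 0.780 is above 0.734 to 0.745. These intervals overlap, so this is weaker evidence than step 1.

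**4. Can each printed figure be reproduced alone?** "intraclass correlation coefficient level 2=0.10" can mean a store variance share of 0.10, or a cumulative figure (store plus group), which with "intraclass correlation coefficient level 3=0.05" leaves a store share of 0.05. In closed form with equal stores of 15 and the group effect cancelling within groups:

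- Share 0.10: variance of a store mean = 0.10 + 0.85/15 = 0.157; SE = √(2×0.157/9) = 0.187; power 0.76 (z) or 0.70 (t, 14 df).
- Share 0.05: variance = 0.05 + 0.90/15 = 0.110; SE = √(2×0.110/9) = 0.156; power 0.89 (z) or 0.84 (t, 14 df).

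With unequal stores (coefficient of variation 0.7), simulated three-level models at d=0.5 give:

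| Store share | z test, known variances | Maximum-likelihood Wald z |
|---|---|---|
| 0.10 | 0.72 to 0.74 | 0.75 to 0.77 |
| 0.05 | 0.845 to 0.853 | 0.865 to 0.872 |

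The first line is near the stress rows and the second near 0.870. No single setting tried gives both. The Wald z test is also anti-conservative here: its simulated type I error was 0.088 at share 0.10, against 0.051 for the planned t-based ANCOVA.

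**5. What does the planned analysis give?** It regresses 18 store means on three group terms, arm and baseline mean, leaving 18 − 3 − 1 − 1 = 13 residual df. Assumptions: two-sided alpha 0.05, gamma store sizes (mean 15, coefficient of variation 0.7, the same at both waves), 3:3 allocation within groups, true variances as weights, d=0.5. The store-level baseline-to-follow-up correlation is not stated, so it is varied. Respondents at the two waves are taken as unrelated.

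| Store share | corr. 0 | 0.5 | 0.8 | 1.0 |
|---|---|---|---|---|
| 0.10 | 0.61 | 0.65 | 0.72 | 0.78 |
| 0.05 | 0.75 | 0.77 | 0.80 | 0.82 |

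Repeat runs gave 0.61 to 0.79 and 0.75 to 0.82. Drawing store sizes separately at each wave lowers the upper ends to about 0.74 and 0.80.

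**6. What would raise it?** If some employees answer both surveys, the within-store sampling errors also correlate. With an assumed correlation of 0.25 and store correlation 0.5 to 1.0, power is about 0.67 to 0.86 (share 0.10) or 0.80 to 0.88 (share 0.05). If the baseline average of 332/18 = 18.4 per store recurs at follow-up, unrelated respondents give about 0.65 to 0.84 or 0.80 to 0.87 over store correlations 0 to 1.

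**The case against.** The strongest reply is that the primary figure may be sound and the secondary rows the faulty ones. Under the cumulative ICC reading a mixed-model Wald test reproduces 0.870. The calculation was based on the primary outcomes, so secondary power below 0.8 contradicts nothing. The ICC convention, the test and the correlation over time are details that an article may leave to a fuller document. Responses are anonymous, but that does not mean different people answer at each wave, and a store-mean ANCOVA benefits from repeat responders without linking them. Baseline also yielded 332 respondents against about 270 planned, and the Sample Size section commits to accounting for a departure from 15 per store.

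Most of this stands, and it limits the point. A reader might infer that the stress rows prove about 74% power for the primary outcomes, or that the design cannot reach 0.8. The documents support neither. The first assumes which rows are wrong. The second holds only for a store share of 0.10 with unrelated respondents and stores of 15.

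The reply does not remove the contradiction. The article prints the table, states one input set for it and draws its conclusion from it. Whichever ICC reading is right, at least one block of rows is wrong under it.

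**Conclusion.** Table 2 is wrong as written: identical stated inputs give 0.870 in two rows and 0.734 to 0.745 in three, a gap of 0.125 to 0.136, and the d column mixes standardised and raw effects. The claim of at least 0.8 is therefore not supported by the stated inputs. It is not refuted either. For the planned analysis at d=0.5 and 15 per store, power is about 0.61 to 0.79 or 0.75 to 0.82, depending on the ICC reading, with unrelated respondents. With a store share of 0.10 it passes 0.8 only with favourable correlation over time or larger stores.

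The contradiction rests only on d being standardised, as its heading says, and on one input set applying to every row. The power ranges rest on the simulation assumptions listed in the working.

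**What to change.** Rerun every row of Table 2 in one simulation of the analysis in Statistical Methods: weighted store-level ANCOVA, group fixed effects, baseline mean, t with 13 df. State one ICC definition. Enter all effects in SD units, so that pain becomes 0.48. Give a range for the baseline-to-follow-up correlation, covering both the store level and repeat responders. Use the same number of runs for all rows, enough that simulation error is small.

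Then replace 0.870 and the sentence claiming at least 0.8 with the resulting range. Alternatively, state the difference detectable with 80% power over the whole correlation range: about 0.52 to 0.63 SD at store share 0.10, 15 per store and unrelated respondents. A line for the achieved baseline store sizes would help.

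The cost is a few hours of simulation and a corrected table and sentence. No extra stores are needed and the analysis does not change. The stated power may become less favourable. The article reports that data have not been viewed, so the correction can be made before analysis.
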